### Follow-up and environmental monitoring

After the baseline survey, follow-up will be conducted to clinically assess the study subjects by means of ACAQ. As timing of administration cannot be predetermined, the occurrence of acute ARIs cases will be assessed on weekly bases in the LTCF and prison, through planned phone contacts with facility study reference personnel. For school setting, cases will be notified by parents through the Influweb platform. For each case a swab will be collected and the ACAQ will be administered.

Since the study population might change due to new entrants or exits during the follow-up, data collection will take into consideration these variations by calculating person/months of observation.

Both air and surface sampling will be carried out monthly, with the possibility of increasing the frequency in case of disease occurrence.

Wastewater samples will be collected weekly.

### Sample size

As this project aims to study several respiratory diseases, it is not feasible to calculate the sample size based on a specific prevalence.

The sample size needed to estimate a prevalence with a fixed margin of error depends on the unknown proportion, with a maximum size at a prevalence of 0.50: assuming this value, we obtain a conservative sample size of 380 to estimate a prevalence with a margin of error of 0.05 with a confidence of 95%.

To achieve this number of subjects, all eligible LTCF residents, people living in prison, students and facility staff who meet the inclusion criteria will be invited to participate in the study.

The number of environmental samples for microbiological and chemical analysis for each target setting and for three sampling points will be one per month for air and surface matrices (approximately 110 samples of air and 110 samples of surface). If clinical cases suspected of ARIs are detected, the number of environmental samples will be increased. Wastewater sampling will be performed monthly for each enrolled setting and for one sampling point (approximately 150 samples).

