### Study design

This is an open, multi-setting, epidemiological cohort, and environmental monitoring study including participants recruited from one LTCF (residents and staff), one remand prison (people living in prison and staff), one primary school (students and teachers). The project spans three years, from December 2022 to December 2025, and is articulated in three distinct phases:

Phase 1 (Dec 2022—Nov 2023) developing study protocol, enrolling facilities, developing data collection instruments (questionnaires and analytical methods for clinical and environmental analyses), obtaining ethics committee approval and engaging target communities (or study participants);Phase 2: (Dec 2023—Nov 2024) conducting field study data collection;Phase 3: (Dec 2024—Nov 2025) processing collected data, developing and validating models, creating information materials and disseminating findings.

The study workflow is shown in **Fig 1**.

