### Statistical analysis and quantitative microbial risk assessment (QMRA)

#### Statistical analysis

Subject characteristics will be described by means of medians and interquartile ranges for numerical variables and absolute frequencies and percentages for categorical variables. The time course of the environmental variables will be presented through graphical displays.

Associations between infections detected via ACAQ and confirmed by clinical swabs (when necessary) and exposure factors detected by the QCB and the environmental air and surface monitoring will be assessed employing logistic regression models taking potential confounders into account. Statistical methods and analysis algorithms will be used to examine the collected data by proximity sensors and identify contact patterns, interaction frequencies and other relevant metrics.

WBE data will be normalised and adjusted to reduce variations arising from excretion and sewage flow. Environmental data will be treated as continuous variables, with regression models featuring splines used to estimate the time course of the measured parameters. The relationship between ARIs incidence and environmental data will be explored via time series regression models. In the event of missing data, imputation models will be employed, and sensitivity analysis will evaluate the impact of outliers on results. All analyses will encompass the entire dataset or stratified by setting. All statistical tests will be two-tailed with a significance level set at α = 0.05. Data analysis will be carried out using the R statistical software [41].

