#### QMRA

QMRA is a formal risk assessment process (based on a modified chemical risk approach) that includes the classical steps of hazards identification and characterization, exposure assessment, and risk characterization. This process involves formulating and applying models using fields and literature data to represent a scenario while addressing uncertainties. QMRA models will be designed and applied to the four selected target viruses and for the different settings in order to assess the risk of ARI based on environmental contamination measured by the microbiological air and surface monitoring. The contamination values, along with the estimated frequency and duration of exposure through inhalation and contact obtained from questionnaires, will be used to calculate the dose, which is the amount of pathogen assumed in a unit of time. Probabilities of infection and disease will then be estimated by applying virus-specific dose-response relationships. These probabilities will be expressed as functions that take into account variability and uncertainties, using Monte Carlo Analysis applied through Vensim software. A sensitivity analysis will also be performed to identify the most influential variables [42].

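### Case-triggered air and surface samples are not separated from scheduled ones, and no rule places exposure before onset, so contamination shed by cases can pass as a predictor

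*Protocol article*

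**What the plan says.** **Sampling.** Air and surface samples are scheduled once a month at three points in each of the three settings, about 110 per matrix (Sample size). On top of that, "If clinical cases suspected of ARIs are detected, the number of environmental samples will be increased". The Follow-up and environmental monitoring section words the same rule more weakly: "Both air and surface sampling will be carried out monthly, with the possibility of increasing the frequency in case of disease occurrence". One passage makes the increase definite and the other makes it optional. Neither gives the number, timing or location of the extra samples.

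**Use of the measurements.** In the Statistical analysis section, associations between infections and exposure factors from the baseline questionnaire and "the environmental air and surface monitoring will be assessed employing logistic regression models taking potential confounders into account". Also, "The relationship between ARIs incidence and environmental data will be explored via time series regression models". In the QMRA section, models are built to "assess the risk of ARI based on environmental contamination measured by the microbiological air and surface monitoring", and the contamination values enter the dose calculation.

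**Analysis set.** "All analyses will encompass the entire dataset or stratified by setting". The article states no split by reason for sampling and no rule on the date of a sample relative to symptom onset. The sensitivity analysis named under Statistical analysis concerns outliers; the one named under QMRA concerns influential variables.

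**The concern.** The exposure is measured more often because the outcome has occurred. The Introduction describes environmental spread as a chain that includes droplet and aerosol emission. A sample taken in response to a case may therefore record what that case shed. If such a sample counts as exposure in a model of infection, the direction of cause is reversed.

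Separately, extra samples in case periods give those periods more weight in any pooled average, spline time course or QMRA contamination distribution.

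This matters because the study's goal is warning before an outbreak (Abstract), and the Discussion gives air and surface monitoring a role in risk assessment before a pathogen enters, with thresholds for intervention. Samples taken because cases have occurred cannot show that contamination comes first.

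**Working it through.** **Inputs from the document:** 3 settings, 3 points, one sample per month per matrix (Sample size); a 12-month field phase, December 2023 to November 2024 (Study design).

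**Assumed, because the document gives no figures:** per-sample positivity of 10% (5% and 20% as a range); 3 extra samples after a case (6 and 9 as a range); shedding that adds s = 0, 0.10, 0.20 or 0.30 to positivity; cases in 25% of weeks. Contamination has no effect on infection throughout, so any association is spurious.

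**1. The plan's own figure.** 3 × 3 × 12 = 108, against about 110 stated. The figure is the fixed schedule alone, and triggered samples come on top. Each facility-month has only 3 scheduled samples per matrix, so 3 extras would double it.

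**2. Trigger alone, continuous exposure.** Mean in a month with a case: (3 × 0.10 + 3 × 0.10)/6 = 0.10. Month without a case: 0.10. There is no bias.

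**3. Trigger plus shedding, continuous exposure.** With the scheduled samples taken before the case, the case-month mean is [3 × 0.10 + 3 × (0.10 + s)]/6 = 0.10 + s/2.

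**4. Over-representation of case periods.** True average positivity is 0.10 + 0.25s. Extras number 3 settings × 13 case weeks (0.25 × 52) × 3 = 117, so the total is 108 + 117 = 225. Pooled positivity is [108 × (0.10 + 0.25s) + 117 × (0.10 + s)]/225.

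| s | Case-month mean (no-case 0.10) | True average | Pooled average |
|---|---|---|---|
| 0.10 | 0.15 | 0.125 | 36.9/225 = 0.164 |
| 0.20 | 0.20 | 0.150 | 51.3/225 = 0.228 |
| 0.30 | 0.25 | 0.175 | 65.7/225 = 0.292 |

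Simulation agrees: pooled 0.165, 0.227 and 0.293. Scheduled samples alone gave 0.126, 0.151 and 0.174, close to the truth.

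**5. Would dropping reactive samples be enough?** Match each sample to its own week's case status. The odds ratio is [(0.10 + s)/(0.90 − s)]/(0.10/0.90) = 2.25, 3.86 and 6.00 for s = 0.10, 0.20 and 0.30, whichever samples are kept. In simulation at s = 0.10 it was 2.28 with scheduled samples only and 2.26 with all. Scheduled samples taken during an outbreak carry shedding too. Only scheduled samples dated before the case removed the association (simulated odds ratio 0.98 to 1.02).

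**6. If exposure were instead any positive sample in the month.** P = 1 − (1 − q)^k grows with the number of samples k even without shedding.
- q = 5%: P = 0.143 at k = 3, then 0.265, 0.370 and 0.460 at k = 6, 9 and 12. Odds ratios against k = 3 are 2.2, 3.5 and 5.1 (a simulation gave 2.2, 3.7 and 4.9).
- k = 6 against k = 3: odds ratio 2.4 at q = 10% (0.469 against 0.271) and 3.0 at q = 20% (0.738 against 0.488).

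**The case against.** A reader might infer that the sampling rule by itself ties contamination to infection and inflates odds ratios two- to fivefold. The document does not support that. The Statistical analysis section treats environmental data as continuous, and on that scale step 2 shows no bias without shedding. The large odds ratios in step 6 need an any-positive summary, which the plan does not prescribe. Such a summary is conceivable, since viral air and surface results are described as presence or detection, but it remains an assumption.

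Other objections also carry weight:

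- Pooling is inferred. The sentence on the entire dataset may mainly concern combining or stratifying settings, and no sentence names the triggered samples. Exposure windows and lags may be set in an analysis plan that is not shown.
- Reverse causation is not peculiar to reactive samples (step 5), so removing them is not a sufficient remedy.
- It does not apply to the QMRA, where contamination shed by cases is the hazard being assessed. There the issue is only how much weight outbreak periods receive.
- Wastewater, to which the Discussion assigns early warning, has no case trigger and is unaffected. The predictive model also draws on wastewater load and individual risk factors, so not every output would be biased.

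These points limit the size and reach of the problem. What stands is a stated outcome-dependent sampling rule, a stated use of those samples as exposure, a whole-dataset rule with no exception, and a transmission chain that includes emission into the environment.

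**Conclusion.** The point holds in a limited form. Followed as written, the plan lets post-case samples count as exposure in models of infection and over-weights outbreak periods in time courses and QMRA inputs. The document does not fix the size, which depends mainly on how much cases shed and how many extras are taken. Under the assumptions above, with contamination causing no infection, the case-month mean is 0.15 to 0.25 against 0.10, and pooled positivity is 0.164 to 0.292 against a true 0.125 to 0.175. With no shedding and a continuous exposure, both effects vanish. The odds ratios of 2.2 to about 5 at 5% positivity should not be quoted as the expected bias. This is an inexpensive improvement to make now, while data collection is under way. The definite and optional wordings of the trigger must also be reconciled.

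**What to change.** - Record for every air and surface sample its date and whether it was scheduled or reactive. Reconcile the Sample size and Follow-up sections on whether extra sampling is fixed or optional.
- In the association and prediction models, use scheduled samples dated before onset, as a lagged exposure. Excluding reactive samples without the timing rule is not enough.
- For the baseline QMRA contamination distribution, use scheduled samples, or weight all samples by the time they represent.
- Report reactive samples separately: as outbreak description, as a labelled QMRA outbreak scenario, or in a sensitivity analysis.

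**Cost.** One data field and some analysis wording; no collected sample is discarded. The main environmental analyses rest on fewer samples. With monthly sampling, a pre-onset measurement can be up to about a month old, which may dilute a true association. The report should state this and the lag used.

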### Data management and storage

All collected data will be pseudonymised, and no sensitive information will be requested from recruited participants.

Pseudonymization will be performed by the LTCF, and prison staff based on investigator-provided unique identifiers lists. For the primary school, this process will be automatically performed by the Influweb platform, which will provide unique identifiers to parents/guardians.

The collected data will be stored in a secure computerised repository for analysis, with paper forms digitally converted. Data collected via the ’Influweb’ platform and ’tag’ devices will be managed directly by platform operators, who will extract the data by means of pseudonymised codes.

Electronic databases will be established and maintained to ensure data security, integrity and reliability, protecting against loss, alteration, or corruption.

The data will be processed in accordance with the provisions of the European Regulation for the processing of personal data no. 2016/679 and Legislative Decree of 30 June 2003 no. 196 ss.ii. as amended by Legislative Decree of 10 August 2018, no. 101 "Provisions for the adaptation of national legislation to the provisions of the GDPR", as well as the Deliberation of the Privacy Guarantor no. 52 of 24 July 2008 and subsequent updates.

The data, processed electronically, will be disseminated only in aggregate and anonymized form, such as through scientific publications, reports, and academic conferences.

### Statistical analysis and quantitative microbial risk assessment (QMRA)

#### Statistical analysis

Subject characteristics will be described by means of medians and interquartile ranges for numerical variables and absolute frequencies and percentages for categorical variables. The time course of the environmental variables will be presented through graphical displays.

Associations between infections detected via ACAQ and confirmed by clinical swabs (when necessary) and exposure factors detected by the QCB and the environmental air and surface monitoring will be assessed employing logistic regression models taking potential confounders into account. Statistical methods and analysis algorithms will be used to examine the collected data by proximity sensors and identify contact patterns, interaction frequencies and other relevant metrics.

WBE data will be normalised and adjusted to reduce variations arising from excretion and sewage flow. Environmental data will be treated as continuous variables, with regression models featuring splines used to estimate the time course of the measured parameters. The relationship between ARIs incidence and environmental data will be explored via time series regression models. In the event of missing data, imputation models will be employed, and sensitivity analysis will evaluate the impact of outliers on results. All analyses will encompass the entire dataset or stratified by setting. All statistical tests will be two-tailed with a significance level set at α = 0.05. Data analysis will be carried out using the R statistical software [41].

#### QMRA

QMRA is a formal risk assessment process (based on a modified chemical risk approach) that includes the classical steps of hazards identification and characterization, exposure assessment, and risk characterization. This process involves formulating and applying models using fields and literature data to represent a scenario while addressing uncertainties. QMRA models will be designed and applied to the four selected target viruses and for the different settings in order to assess the risk of ARI based on environmental contamination measured by the microbiological air and surface monitoring. The contamination values, along with the estimated frequency and duration of exposure through inhalation and contact obtained from questionnaires, will be used to calculate the dose, which is the amount of pathogen assumed in a unit of time. Probabilities of infection and disease will then be estimated by applying virus-specific dose-response relationships. These probabilities will be expressed as functions that take into account variability and uncertainties, using Monte Carlo Analysis applied through Vensim software. A sensitivity analysis will also be performed to identify the most influential variables [42].

### Outcomes of the study

The impact of ARIs is greatest in fragile and disadvantaged populations [43]. Our project has a clear public health focus: to reduce incidence of ARIs, limit their economic burden on the NHS, and address inequalities in disease burden related to age and marginalisation. While the protocol is developed and piloted within selected facilities in Tuscany Region, the methodology applied, and the findings can be generalised at national/international levels in similar settings. The expected outcomes corresponding to each specific objective are detailed below.

Sentinel clinical surveillance system for acute respiratory diseases will be established, with data collection tools (questionnaires) for clinical surveillance and risk factors tested and validated in different indoor settings such as LTCFs, prisons, and schools.Indoor air quality assessment instruments and tools will be validated in the above-mentioned settings. Additionally, methods and strategies for assessing air and surfaces microbial contamination will be validated in the same settings. Methods and strategies for WBE will also be validated for the same selected communities.An integrated environmental and clinical surveillance system will be established and tested for closed settings. This will involve:
Assessing the connection between respiratory disease incidence, environmental and individual risk factors, and wastewater viral load. A predictive model using a nomogram will be developed, validated, and applied;Validating a QMRA model for different viruses and settings;Providing recommendations for expanding the integrated surveillance system of ARIs for early warning and pandemic preparedness efforts.

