This study may have limitations. Coordinating data collection across such different settings presents logistical and coordination challenges. A complete correlation between clinical and environmental data could not be representative in case of limited data collection due to insufficient number of study subjects providing informed consent (e.g. refusal to undergo to nasopharyngeal swabs) or higher than expected loss to follow-up. This study potentially demands sustained participant engagement and ongoing data collection, which may discourage prospective participants, especially those in vulnerable situation, as well as parents of school children. Additionally, privacy concerns related to individual data collection and management, especially in a school environment, may reduce participants’ confidentiality and trust. Another limitation lies in the large variability of environmental conditions and individual behaviours across the different settings analysed, potentially affecting the generalizability of the findings to other context. Finally, while innovative, reliance on advanced analysis techniques and biomolecular PCR tests could pose challenges in terms of expertise required for implementing this approach across various setups.

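### The plan says its findings generalise nationally and internationally, but one facility per setting type in one field year cannot show this

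*Protocol article*

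**What the plan says.** All references are to the protocol article.

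- **Facilities (Study design; details in Study setting and participants).** Participants come from "one LTCF (residents and staff), one remand prison (people living in prison and staff), one primary school (students and teachers".
- **Time (Study design).** There is one field phase: "Phase 2: (Dec 2023—Nov 2024) conducting field study data collection". Phase 3 then covers "processing collected data, developing and validating models". No further data collection is described.
- **Claim (Outcomes of the study).** After noting that the work is piloted in selected Tuscan facilities, the same sentence says that "the methodology applied, and the findings can be generalised at national/international levels in similar settings". The list of outcomes adds: "A predictive model using a nomogram will be developed, validated, and applied".
- **Objective (Aim, Obj. 3).** Risk prediction models are meant to be transferable to similar settings, up to international level.
- **Discussion.** One paragraph counts the variety of settings as a gain in transferability. The limitations paragraph names large variability across those settings as "potentially affecting the generalizability of the findings to other context".
- **Analysis (Statistical analysis).** Analyses use the whole dataset or are stratified by setting.

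**The concern.** Generalising to similar settings means saying something about other LTCFs, other prisons and other schools. That requires some idea of how much such facilities differ from one another in incidence, in environmental conditions and in the relation between the two. This design offers none. Whatever is seen in the LTCF may belong to LTCFs in general or to this one building, and the data cannot separate the two. The same holds for the prison and the school.

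At stake is what the study may conclude. A reader who meets a validated model next to findings said to generalise could take performance in other facilities as already tested. The limitations paragraph does not prevent this. It attributes the doubt to differences across the three settings and does not mention that each type is represented once.

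**Working it through.** **Inputs.** Facilities per type: 1, so 3 in all (Study design). Field phase: 12 months (Study design). Planned size 380, prevalence 0.50, margin 0.05, confidence 95% (Sample size). The intra-facility correlation (ICC) is not given; 0.01 to 0.10 is my assumption, for illustration only.

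**1. The plan's own figure.** For a single proportion, n = z² p(1 − p) / d² = 1.96² × 0.25 / 0.05² = 384.1, rounded up to 385. The stated 380 is within 3% of this. At 380 the margin is 1.96 × √(0.25/380) = 0.0503. The arithmetic is sound, but the formula treats participants as one simple random sample and has no between-facility term.

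**2. Between-facility variation within a type.** Degrees of freedom = facilities of that type − 1 = 1 − 1 = 0. The number of participants does not enter, so more recruitment does not help. Stratifying by setting does not help either, because each stratum is one facility.

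**3. Pooling the three (illustration).** Suppose, generously, that the three were a random sample of closed communities of one kind, with m = 380/3 ≈ 126.7 people each. The design effect is 1 + (m − 1) × ICC and the effective size is 380 divided by it. The margin is the multiplier × √(0.25 × design effect / 380), with multiplier 1.96 (normal) or 4.303 (t on 3 − 1 = 2 degrees of freedom).

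| Assumed ICC | Design effect | Effective size | Margin, normal | Margin, t on 2 df |
|---|---|---|---|---|
| 0.01 | 2.26 | 168 | 0.076 | 0.17 |
| 0.05 | 7.28 | 52 | 0.136 | 0.30 |
| 0.10 | 13.57 | 28 | 0.185 | 0.41 |

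Even in this favourable reading, the margin for a wider population of facilities is several times the 0.05 in the plan. The three facilities differ in type by design, so the pooled calculation is not a substitute for step 2.

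**4. Time.** Twelve months from December to November contain each calendar month once per facility. Validation in a separate year is not possible with these data. Holding out later months is possible, but it also changes the season, so it tests less than a repeat year would.

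**5. The statements side by side.** Outcomes of the study asserts that findings generalise. Objective 3 and one paragraph of the Discussion point the same way. The limitations paragraph says generalisability may be affected. These are in tension, and only the last fits steps 2 to 4.

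**The case against.** The other side has several fair points.

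- **Methods are not findings.** The sentence covers both. Questionnaires, sampling procedures and PCR protocols can be reused without several facilities per type, and the risk assessment (QMRA) draws partly on literature data and virus-specific dose-response relations. This stands; only the claim about findings needs narrowing.
- **The nomogram.** A reader might infer that one year in three facilities cannot support any validated model. The documents do not bear that out. They say validated, not externally validated; internal validation is feasible on these data; and its details may sit in an analysis plan that is not shown.
- **Within-facility signal.** Environmental predictors vary over time through monthly air and surface samples, repeated wastewater samples and continuous sensors, and the plan uses time series regression. Zero degrees of freedom therefore do not prevent fitting a model. They bear on carrying it to another facility. This also stands.
- **Pilot status and caveat.** The work is called a pilot, the claim is limited to similar settings, and the limitations paragraph is hedged and speaks of other contexts. The passages are thus in tension rather than in flat contradiction. But the pilot remark opens the very sentence that then claims generalisable findings, so it does not cure that claim.
- **Use elsewhere.** A reader might infer that an untested alarm rule will be put into service in other facilities. No such deployment is planned; the outcomes promise recommendations for expanding the system.

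**Conclusion.** The point holds for the findings. The plan claims a property that its design lacks: one facility per type gives 0 degrees of freedom for between-facility variation at any sample size, and there are no external validation data from another facility or season. This conclusion rests only on the stated number of facilities and the stated field phase. The pooled margins of 0.17 to 0.41 depend on the assumed ICC and on equal facility sizes, and they serve only as illustration.

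The point does not extend to the sample-size arithmetic, which reproduces, to the transfer of the methods, or to internal validation of the nomogram. An analysis plan not shown here could settle how the model is validated internally, but it could not add a second facility of any type to these data.

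**What to change.** 1. **Outcomes of the study.** Limit the claim to the methods. For example: *The methods may be transferable to similar settings. The findings are pilot estimates for the three participating facilities and need external validation in other facilities and seasons.*
2. **Aim (Obj. 3) and the Discussion's transferability statement.** Align both with the limitations paragraph, and add to that paragraph that each setting type is represented by one facility in one field year.
3. **Nomogram.** Describe it as internally validated. Report optimism-corrected calibration and discrimination, plus a check with later months held out, noting that the held-out months also differ in season. The resampling details can be left to the analysis plan.
4. **Leave-one-setting-out, if reported.** Label it a cross-setting stress test. Predicting the LTCF from the prison and the school says nothing about another LTCF. Restrict it to predictors collected in all three settings, which excludes the contact sensors worn only by students.

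The cost is some rewording and a little extra analysis of data already planned, with no change to data collection. The downside is a more modest claim.

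If the wider claim is to be kept, it needs data from further facilities of each type and at least one more season, which is a different study.
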